## Abstract

This study protocol aims to explore the effectiveness, safety, and cost-effectiveness of a herbal medication,* Gongjindan* (GJD), in patients with chronic dizziness. This will be a prospective, multicenter, randomized, double-blind, placebo-controlled, parallel-group, clinical trial. Seventy-eight patients diagnosed with Meniere's disease, psychogenic dizziness, or dizziness of unknown cause will be randomized and allocated to either a GJD or a placebo group in a 1 : 1 ratio. Participants will be orally given 3.75 g GJD or placebo in pill form once a day for 56 days. The primary outcome measure will be the Dizziness Handicap Inventory score. Secondary outcome measures will be as follows: severity (mean vertigo scale and visual analogue scale) and frequency of dizziness, balance function (Berg Balance Scale), fatigue (Fatigue Severity Scale) and deficiency pattern/syndrome (qi blood yin yang-deficiency questionnaire) levels, and depression (Korean version of Beck's Depression Inventory) and anxiety (State-Trait Anxiety Inventory) levels. To assess safety, adverse events, including laboratory test results, will be monitored. Further, the incremental cost-effectiveness ratio will be calculated based on quality-adjusted life years (from the EuroQoL five dimensions' questionnaire) and medical expenses. Data will be statistically analyzed at a significance level of 0.05 (two-sided). This trial is registered with ClinicalTrials.gov NCT03219515, in July 2017.

## 1. Introduction

Dizziness is a typical manifestation of various neurological diseases. It is mostly related to vestibular disorders of the inner ear, such as benign paroxysmal positional vertigo (BPPV), vestibular neuritis, or Meniere's disease (MD) [1]. However, the symptom may also arise from some conditions involving the central nervous system (e.g., cerebral stroke, vertebrobasilar insufficiency), cardiovascular diseases (e.g., arrhythmia, orthostatic hypotension) [2], or even certain psychiatric conditions [3]. In some cases, chronic and recurrent dizziness fails to receive a diagnosis and remains as unspecified or undefined dizziness in clinical records.

According to studies investigating the etiology of recurrent dizziness, 12.5% of cases were attributed to MD [4], 15% to psychogenic dizziness [5], and 10–52% to dizziness of unknown cause [5, 6]. Public healthcare data systems also show the incidence of dizziness has increased by approximately 20% in the past 5 years [7].

Otorhinolaryngologists prescribe vasodilators or diuretics to patients with MD. For example, betahistine is frequently used as a full agonist of the H1 receptors located in blood vessels in the inner ear, which can increase local vasodilation and help alleviate symptoms [8]. Moreover, diuretics are sometimes used to treat endolymphatic hydrops. However, there is no confirmatory evidence of the utility of these treatments [4]. For psychogenic dizziness, psychiatrists administer to patients antianxiety agents or antidepressants, accompanied by cognitive-behavioral therapy [3], which also lack clinical verification. If the dizziness is due to unknown causes, drugs, such as meclizine, clonazepam, or lorazepam, or rehabilitation therapy is prescribed, which mostly rely on anecdotal evidence [6].

Due to these limitations, many patients with dizziness visit practitioners of traditional medicine in Korea. Traditional Korean Medicine (TKM) doctors prescribe various herbal medications to these patients, based on syndrome/pattern identification [9].* Gongjindan* (GJD) is one of the most preferred options. A classic Korean book of traditional medicine,* Dongeuibogam*, suggests that GJD can be prescribed for liver-deficiency syndrome/pattern with symptoms of dizziness/vertigo, dim eyes, a pale face, and/or weak muscles [10, 11]. However, the modern scientific level of the evidence for GJD remains low.

Most studies have been* in vivo* or* in vitro* experiments that have demonstrated the efficacy of GJD in ameliorating memory impairments [12, 13] or fatigue [14], its antioxidant effects [15], neuroregulatory effects for transient middle cerebral artery occlusion [16] or Alzheimer's disease [17], and lipid-lowering effect in hyperlipidemia [18]. Clinical studies have been rarer. A retrospective study for Alzheimer's disease [19] and a case report for dizziness of patients with anemia [20] have been published. Only one randomized controlled trial (RCT) with GJD has so far been planned with fatigue patients [21], which has not announced its results yet. Therefore, the effectiveness of GJD should be explored clinically with qualified RCTs using a placebo for comparison. This study would be the first RCT for chronic dizziness to explore the clinical effectiveness, safety, and cost-effectiveness of a herbal drug, GJD pills.

This study protocol is primarily aimed at exploring the effectiveness of GJD in patients with chronic dizziness, compared to placebo. Additionally, the safety and cost-effectiveness of GJD will be investigated.

## 2. Materials and Methods

This study protocol has been designed to conform with Standard Protocol Items: Recommendations for Interventional Trials (SPIRIT), 2013 statement [22], and the elaborated Consolidated Standards of Reporting Trials (CONSORT) statement for herbal interventions [23].

### 2.1. Objectives and Hypothesis

The primary objective of this study is to evaluate the effect of GJD administration for 8 weeks, compared to placebo, on chronic dizziness (MD, psychogenic dizziness, or dizziness of unknown cause). The alternative hypothesis is that the mean difference between Dizziness Handicap Inventory (DHI) scores at baseline and endpoint in the GJD group will not be equal to that in the placebo group.

Additionally, the changes in dizziness severity and frequency will be evaluated with validated scales. Further, the levels of fatigue, depression, anxiety, and quality of life (QoL) will be compared between the two groups posttreatment. The safety of GJD administration will be examined based on laboratory tests and adverse events (AEs). Finally, the cost-effectiveness of GJD will be evaluated with quality-adjusted life years (QALY).

### 2.2. Study Design

This study will be a prospective, multicenter, randomized, double-blind, placebo-controlled, parallel-group, clinical trial. Seventy-eight patients diagnosed with MD, psychogenic dizziness, or dizziness of unknown cause, with a DHI score ≥ 24 at baseline, and having complained of dizziness for more than 1 month will be randomized and allocated to either the GJD or placebo group in a 1 : 1 ratio. They will be orally given 3.75 g GJD or placebo in pill form once a day for 8 weeks (56 pills in total). To collect data for the cost-effectiveness analysis, we will follow up the patients for up to 12 months from randomization. The study flowchart is displayed in diagram form in Figure 1 and the specified timetable is presented in Table 1.

### 2.3. Setting and Recruitment

Four TKM hospitals in the Republic of Korea, that is, Kyung Hee University Korean Medicine Hospital in Seoul, Dongguk University Ilsan Oriental Hospital in Goyang (Gyeonggi-do), Pusan National University Korean Medicine Hospital in Yangsan (Gyeongsangnam-do), and Semyung University Korean Medicine Hospital in Chungju (Chungcheongbuk-do), will enroll eligible participants. Participants will be recruited mostly from the respective outpatient clinics. Moreover, study advertisements will be posted on webpages and notice boards.

### 2.4. Ethical Review and Trial Registration

This protocol (version 2.5) and the informed consent forms have been peer-reviewed and approved by the Institutional Review Board of Kyung Hee University Korean Medicine Hospital (approval number KOMCIRB-170417-HRBR-012) following the scientific content and ethical compliance with regulations, that is, Good Clinical Practice and relevant laws by Ministry of Food and Drug Safety in Korea. The study has been registered at ClinicalTrials.gov in July 2017 (identifier: NCT03219515).

### 2.5. Eligibility Criteria

Participants will be included if they satisfy all of the following criteria:Age between 20 and 79 years, of either sexDizziness originating from MD, psychogenic cause, or unknown causeRecurring symptom of dizziness for more than 1 monthDHI score ≥ 24 at baselineLiver-deficiency pattern/syndrome identified by TKM doctorsWillingness to provide written informed consent.

The targeted scope of chronic dizziness has been established based on a preceding acupuncture trial [24]. The liver-deficiency syndrome is defined as having all of the main symptoms and at least two of the secondary symptoms [10, 25]. The main symptoms include dizziness, dim eyes, and pale face. The secondary symptoms include lack or a momentary loss of vision, numbness at extremities, muscular spasm, twitching and/or cramping, hypochondriac pain, dry or pale fingernails, toenails, or lips, tinnitus, and scant menstruation. Two TKM doctors who have 1 year or more of clinical experience will independently identify the pattern/syndrome, and only the patients diagnosed with consistent liver-deficiency pattern/syndrome will be enrolled in the study.

Participants will be excluded if any of the following criteria is applicable:Dizziness attributable to vestibular disorders (e.g., benign paroxysmal positional vertigo, peripheral vestibulopathy, labyrinthitis, and vestibular neuronitis)Dizziness attributable to central nervous system (CNS) disorders (e.g., cerebellar ataxia, stroke, demyelination, vertebrobasilar insufficiency, seizure, increased intracranial pressure, Parkinson's disease, and migraines)Cervicogenic dizzinessDizziness attributable to cardiovascular disorders (e.g., arrhythmia, heart valvular disease, anemia, orthostatic hypotension, and coronary artery disease)Any active or uncontrolled disease that might cause dizziness (e.g., uncontrolled diabetes mellitus, hypertension, and respiratory or endocrinological disorders)Dizziness attributable to medication side effectsSevere chronic or terminal diseases (malignant cancer, tuberculosis, etc.)Intake of antivertiginous drugs that cannot be discontinuedFollowing physiotherapy, manual therapy (e.g., vestibular rehabilitation), and/or cognitive-behavioral therapy for the treatment of dizzinessAspartate aminotransferase (AST), alanine aminotransferase (ALT), blood urea nitrogen (BUN), or creatinine > 3 × upper limit of normal range at baselineWomen of (suspected) pregnancy or breast-feedingAllergic reactions to the study medicationsSuspicion of alcohol and/or drug abuseEnrollment in another clinical study presently or within 30 days prior to the initial administration of the study medicationsDifficulty in reliably communicating with the investigators or likelihood of inability to follow instructionsReasons for ineligibility of participation judged by investigators.

### 2.6. Dropout Criteria

Already enrolled participants will be dropped out if they withdraw their consent for participation, are lost to follow-up, cannot continue participation due to adverse events or complications, consume disallowed medications, or markedly deviate from the study protocol.

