### 2.10. Concomitant Medications

All of the concomitant medications will be recorded throughout the trial. No other drugs (betahistine, difenidol, flunarizine, cinnarizine, dimenhydrinate, gingko, meclizine, metoclopramide, scopolamine, pentoxifylline, perphenazine, ergoloid mesylate, droperidol, phenobarbital, prochlorperazine, promethazine, trimethobenzamide, or vertigoheel, etc.) or herbal drugs to manage the symptom of dizziness will not be allowed. Moreover, other therapies for dizziness, like physical therapy, rehabilitation, acupuncture, electroacupuncture, pharmacoacupuncture, moxibustion, cupping, and cognitive-behavioral therapies, will be disallowed during the study.

The following drugs, which can induce drug-related dizziness, will be closely monitored: *α*1-adrenergic antagonists, alcohol, aminoglycosides, anticonvulsants, antidepressants, anti-Parkinson medication, antipsychotics, *β*-blockers, calcium channel blockers, class 1a antiarrhythmics, digitalis glycosides, diuretics, narcotics, oral sulfonylurea, vasodilators, anticoagulants, antidementia agents, antihistamines (sedating), antirheumatic agents, anti-infectives (anti-influenza agents, oral antifungals, quinolones), antithyroid agents, anxiolytics, attention-deficit/hyperactivity disorder agents, cholesterol-lowering agents, bronchodilators, skeletal muscle relaxants, urinary and gastrointestinal antispasmodics, and so on.

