#### 2.12.5. Cost-Effectiveness Assessment

The EuroQoL five dimensions' questionnaire (EQ-5D), consisting of two parts, that is, EQ-5D-5L and EQ VAS, will be used to assess quality of life, based on which QALY will be calculated. The Korean version of EQ-5D scale has been studied on its validity and reliability [57]. Also, direct costs (medical and nonmedical expenses) incurred in treating dizziness during the treatment (8 weeks) and follow-up (up to 12 months from randomization) periods will be investigated (Table 1). Medical fee signifies the cost paid in hospitals or clinics. Nonmedical fee signifies transportation and time costs that patients would incur for dizziness treatment. Based on the calculated QALY and fees, the incremental cost-effectiveness ratio (ICER) will be estimated (ICER = Δ  cost/Δ effectiveness). The ICER signifies the amount of cost necessary to improve by 1 unit of effectiveness.

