### 2.13. Sample Size Calculation

To calculate the effect size, we used a preceding RCT on acupuncture therapy for MD with DHI assessment, as there have been no clinical studies for GJD effectiveness in chronic dizziness [58]. The null hypothesis is that *μ*_GJD_ = *μ*_placebo_, while the alternative hypothesis is *μ*_GJD_ ≠ *μ*_placebo_, where *μ* denotes the mean difference of DHI score between the baseline and endpoint. With the mean difference (−3.63) and the standard deviation (4.84), under the assumption of correlation coefficient (0.1), the sample size was calculated as 29 per group (two-sided, *α* = 0.05 and 1 − *β* = 0.8). Therefore, we are going to recruit 78 participants for both groups (39 per group) under a 25% anticipated dropout rate.

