### 2.14. Statistical Analysis

The primary and secondary variables for the effect assessments will be statistically analyzed by analysis of covariance (ANCOVA) or rank ANCOVA with group and site as covariates. If any demographic characteristics show significant difference between groups, those variables will also be used as covariates. When there is a significant interaction between diagnosis (MD, psychogenic dizziness, or dizziness of unknown cause) and group, subgroup analysis will be performed.

The confidence interval (CI) of BI will be addressed and blinding will be deemed successful when the CI includes the zero value. For safety assessment, the chi-squared test or Fisher's exact test will be performed with the proportions of AEs, while lab results will be compared between groups by chi-squared test (proportions of abnormal results) or McNemar's test (before-and-after comparison within a group). An independent statistician ([name]) will analyze any data with a significance level of 0.05 (two-sided) with SAS 9.4 software (SAS Institute Inc.).

The primary analysis will be performed with the full analysis set, which is defined as the group of participants who were prescribed at least once or more the GJD or placebo pills and for whom DHI was evaluated more than once. The missing data will be imputed with the last observation carried forward method. The per protocol set will be additionally analyzed, which includes only the participants who complete all the scheduled visits. We are going to include any participants who took at least one pill of the study drugs for the safety assessment.

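### Section 2.6 drops participants who take a disallowed drug or markedly deviate and provides for no later assessment; followed as written, it forfeits DHI, EQ-5D and cost data that could have been collected

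*Protocol article*

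**What the plan says.** Section 2.6 (Dropout Criteria) is one sentence. It begins "Already enrolled participants will be dropped out if they withdraw their consent for participation, are lost to follow-up" and goes on to those who "cannot continue participation due to adverse events or complications, consume disallowed medications, or markedly deviate from the study protocol". All five reasons have the same consequence.

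Section 2.10 (Concomitant Medications) bars other dizziness drugs and states that "herbal drugs to manage the symptom of dizziness will not be allowed".

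Section 2.2 (Study Design) gives the purpose of the long follow-up: "To collect data for the cost-effectiveness analysis, we will follow up the patients for up to 12 months from randomization". Section 2.12.5 counts direct costs "incurred in treating dizziness during the treatment (8 weeks) and follow-up (up to 12 months from randomization) periods". Table 1 schedules DHI to V6 (day 56), and EQ-5D and cost information to V9 (month 12).

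Section 2.13 allows for losses: "we are going to recruit 78 participants for both groups (39 per group) under a 25% anticipated dropout rate". Section 2.14 fills the gaps: "The missing data will be imputed with the last observation carried forward method". It keeps anyone with study pills prescribed and DHI evaluated more than once in the full analysis set, and defines the per protocol set by completion of all visits.

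**The concern.** Consent withdrawal and loss to follow-up end data collection whatever the protocol says. Taking a disallowed drug or deviating from the protocol does not: the participant can usually still be seen. Putting all of these under one rule discards data that could have been obtained.

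The loss is unlikely to be random. The disallowed drugs are those used to treat dizziness, so a participant who takes one has plausibly not improved or has worsened. Three things are at stake:

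- **Cost-effectiveness.** Section 2.12.5 wants the cost of treating dizziness during the 8 weeks and afterwards, yet taking a dizziness drug in those 8 weeks is itself a reason for removal. For these participants, 12-month QALYs and costs would rest almost wholly on imputation, or the participants would be excluded.
- **Primary endpoint.** The day-56 DHI is replaced by an earlier score.
- **Later options.** DHI regardless of other treatment could not be analysed for these participants, even as a sensitivity analysis. No later analysis plan can recover scores that were never collected.

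**Working it through.** **The plan's own figure.** With a difference of 3.63 and an SD of 4.84 (section 2.13), the standardised effect is 3.63/4.84 = 0.75. A two-sided two-sample t-test at 0.05 with 80% power needs 28.90, so 29 per arm. With 25% dropout, 29/0.75 = 38.7, rounded up to 39 per arm and 78 in total. The stated figures reproduce. The allowance is 39 − 29 = 10 per arm for all causes; section 2.13 does not split it by reason. The lost numbers are therefore budgeted for, and the issue is which data are lost.

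**Scheduled assessments (Table 1).** Post-baseline DHI: V3, V4, V5, V6 (4). EQ-5D: V2, V4, V6, V7, V8, V9 (6). Cost information: V3 to V9 (7).

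**Loss per dropped participant, by last visit attended.**

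| Last visit | DHI lost | EQ-5D lost | Cost lost | Year between observed EQ-5D values | Year covered by costs |
|---|---|---|---|---|---|
| V3 (day 14) | V4–V6: 3 of 4 | V4, V6–V9: 5 of 6 | V4–V9: 6 of 7 | 0/365 = 0% | 14/365 = 3.8% |
| V4 (day 28) | V5–V6: 2 of 4 | V6–V9: 4 of 6 | V5–V9: 5 of 7 | 28/365 = 7.7% | 28/365 = 7.7% |
| V5 (day 42) | V6: 1 of 4 | V6–V9: 4 of 6 | V6–V9: 4 of 7 | 28/365 = 7.7% | 42/365 = 11.5% |

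If LOCF also applies to EQ-5D, which the article does not say, a day-0 or day-28 value stands for the remaining 92% to 100% of the year.

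**How many.** Assume that 1 to 5 of the 10 allowed dropouts per arm are for these two reasons. That is 2 to 10 participants: 2/78 = 2.6% to 10/78 = 12.8%.

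**Shift in the DHI contrast.** Let k be the number of extra removals in one arm and d the change in DHI between the carried score and day 56. That arm's mean moves by k × d/39. Assume d = 2 to 10 points.

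- k = 1: 2/39 = 0.05 to 10/39 = 0.26 points, or 1.4% to 7.1% of the planned 3.63.
- k = 3: 6/39 = 0.15 to 30/39 = 0.77 points, or 4.2% to 21.2% of 3.63.
- Equal removals and equal d in both arms: no shift.

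**The case against.** The strongest reply is that the harm is inferred. No sentence says that visits stop, the article condenses a fuller protocol that is not shown, and section 2.2 promises 12 months of follow-up without excepting those who stop treatment. LOCF and the 25% allowance would be needed for genuine withdrawals anyway. This stands as a limit on certainty. It does not remove the point, because the article states the rule itself, words it around participation and not pill-taking, and groups these events with two after which no data can be had. Whether participants continue to be seen is a matter of trial conduct, not a detail for an analysis plan.

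A second reply is that sections 2.6 and 2.12.5 do not contradict each other: participants who take no disallowed drug also incur dizziness costs. That is correct. The rule removes a subset with extra treatment to cost, not everyone with costs. Section 2.6 names only medications, so non-drug care leads to removal only if judged a marked deviation. The problem is confined here to the 8 weeks, since section 2.12.5 plans to cost dizziness treatment afterwards and Table 1 records concomitant medication only to V6.

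A third reply is that the magnitude is largely assumed. For the number affected and the DHI shift this is true, and the 21.2% needs both the largest d and a three-person imbalance. The visit counts come straight from Table 1 and depend only on the reading of section 2.6. Dropped participants also stay in the full analysis set if DHI was evaluated more than once, and nothing discards their earlier data.

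**Conclusion.** The concern holds, with medium confidence. Followed as written, section 2.6 gives up obtainable data. A participant removed after V3, V4 or V5 loses 1 to 3 of 4 post-baseline DHI scores, 4 or 5 of 6 EQ-5D and 4 to 6 of 7 cost records, and at most 11.5% of the year is observed. This rests on reading the rule as ending visits.

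The main damage is to the 12-month cost-effectiveness analysis, which is an additional aim. For the primary DHI contrast the size and direction of any bias are unknown: 0.05 to 0.77 points under the assumptions above, and zero if removals and later changes are equal across arms. The sample size is unaffected. The point merits a change to the protocol, but it does not undermine the trial.

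**What to change.** Amend section 2.6 so that a disallowed medication, a marked deviation or an adverse event may end the study pills but does not end follow-up. Unless consent is withdrawn, collect DHI to V6 and EQ-5D and costs to V9 at the scheduled visits, and record the other treatment with its dates. State before unblinding whether DHI observed after other treatment enters the primary analysis or a sensitivity analysis.

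One consequential change is needed. The per protocol set is defined by visit completion, so under the amended rule these participants could qualify for it. Exclude those with disallowed treatment or a major deviation explicitly.

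The cost is a short amendment and some effort to retain participants who have stopped the pills. No visits are added and the sample size stays at 39 per arm.

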### 2.7. Randomization, Allocation, and Blinding

An independent statistician ([name]) will generate random sequence numbers via SAS® 9.4 software (SAS Institute Inc., Cary, NC). Stratified randomization will be performed in blocks in order to keep the sizes of both arms similar with the strata of the study sites. The random number table will be delivered from the statistician to a pharmaceutical company, where GJD and placebo pills will be produced.

The investigational products labeled with random codes will be provided to a pharmacist, who will dispense them to the enrolled participants. According to the order of enrollment, participants will be allocated to either the GJD group or the placebo group in a 1 : 1 ratio. As only the statistician and the pharmaceutical company will have access to the random table throughout the study, allocation will stay concealed.

Since we are going to use placebo pills that look, taste, and smell similar to GJD pills, both investigators and patients will stay blinded until the completion of the study. Only clinical emergency due to serious AEs will break the code and blinding.

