## 3. Results and Discussion

This study is a prospective, multicenter, randomized, double-blind, placebo-controlled, parallel-group, clinical trial to explore the effectiveness, safety, and cost-effectiveness of a herbal drug, GJD, for patients with chronic dizziness attributable to MD, psychogenic dizziness, or dizziness of unknown cause. We are going to administer to patients GJD or placebo pills for 8 weeks and follow them up for 12 months. Four TKM hospitals in Korea will enroll 78 participants.

Dizziness may ensue from a variety of central or peripheral diseases and in some cases as a drug complication. This may complicate the diagnostic process. This study will include patients diagnosed with MD, psychogenic dizziness, or dizziness of unknown cause, which may create an issue with homogeneity. However, there were previous clinical studies which also focused on the symptom of dizziness with varied origin to demonstrate new efficacy [28, 35], including an acupuncture study for chronic dizziness [24], which has meaningfully been referred for this trial.

GJD is a widely prescribed herbal pill in Korea, but it is mostly used for patients with severe deficiency pattern/syndrome, especially those complaining of marked fatigue [14, 21]. However, based on the seminal work* Dongeuibogam* [10], we expect GJD to also manage chronic dizziness.

This RCT included various diseases (MD, psychogenic dizziness, or dizziness of unknown cause) inducing dizziness, which might reduce the level of homogeneity of patient population. The investigators discussed this issue, which might affect significantly the study results in the future. However, it was taken into consideration that this trial should reflex the real clinical practices as much as possible, which means that GJD is a herbal drug and it has been described based on pattern/syndrome identification in TKM. So, we think the screening process is one of the key parts for this trial to include eligible participants. Investigators and coordinators should be trained with written standard operating procedures for the trial before enrolling the first participants, since this study is a multicenter trial, to control the high quality throughout the whole process. Also, an independent monitor will regularly visit all the hospitals for auditing ethical and scientific issues.

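### Diagnosis, known before randomisation and named by the protocol as a possible influence on the results, never adjusts the treatment estimate; it should be a prespecified factor in the ANCOVA

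*Protocol article*

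**What the plan says.** All references are to the protocol article.

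- Section 2.5 admits three kinds of dizziness: Meniere's disease, psychogenic and unknown cause. The diagnosis is therefore on record before randomisation.
- Section 2.7, allocation: "Stratified randomization will be performed in blocks in order to keep the sizes of both arms similar with the strata of the study sites". Site is the only stratum.
- Section 2.14, primary and secondary variables: "analysis of covariance (ANCOVA) or rank ANCOVA with group and site as covariates".
- Section 2.14, further covariates: "If any demographic characteristics show significant difference between groups, those variables will also be used as covariates".
- Section 2.14, the one use of diagnosis: "When there is a significant interaction between diagnosis (MD, psychogenic dizziness, or dizziness of unknown cause) and group, subgroup analysis will be performed".
- Section 3, on pooling: "This RCT included various diseases (MD, psychogenic dizziness, or dizziness of unknown cause) inducing dizziness, which might reduce the level of homogeneity of patient population". It goes on: "The investigators discussed this issue, which might affect significantly the study results in the future".

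**The concern.** The plan singles out diagnosis as something that may influence the results, but no part of the main analysis adjusts for it. It is not in the stated model. It cannot come in by the extra-covariate rule, because a diagnosis is not a demographic characteristic. The interaction test answers another question: whether the effect of treatment differs between diagnoses. It does not correct the overall estimate when one arm happens to contain more patients of a diagnosis that improves more, or less, whatever pill they take.

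Two things are at stake, both only so far as diagnosis predicts change in DHI. Variation between diagnoses stays in the error term and costs power, in a trial sized with almost no slack. And with 39 patients per arm, a chance difference in case mix moves the estimate in the trial actually run.

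**Working it through.** **1. The plan's own figure.** Section 2.13 gives a difference of 3.63, SD 4.84, two-sided 0.05, 80% power, 29 per group and 25% dropout. The two-sample noncentral t gives power 0.787 at 28 per group and 0.801 at 29. Then 29/0.75 = 38.7, so 39 per group and 78 in total. The plan's numbers reproduce if 4.84 is the SD of the change score, which is how it is used below.

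**2. Precision gained by adjustment.** Let R² be the share of the variance of DHI change explained by diagnosis. The document does not give it, so it is an assumption shown as a range. Here 4.84 is the total SD.

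Adjusted SD = 4.84 × √(1 − R²); SE = SD × √(2/29). Residual degrees of freedom with group, four sites and three diagnoses: 58 − 1 − 1 − 3 − 2 = 51.

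| R² | SE of the difference | Power at 29 per group |
|---|---|---|
| no adjustment | 1.27 | 80.1% |
| 2% | 1.26 | 80.8% |
| 5% | 1.24 | 82.0% |
| 10% | 1.21 | 84.0% |
| 20% | 1.14 | about 88% |

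If R² is zero, power stays at about 80%: losing 2 degrees of freedom out of more than 50 is negligible.

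**3. Shift from chance imbalance.** Assumptions:

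- mean DHI change of 0 for Meniere's disease, 5 for psychogenic dizziness and 2.5 for unknown cause;
- within-diagnosis SD 4.84 (the planning trial enrolled Meniere's disease only);
- case mix 12.5 : 15 : u with u = 10, 31 or 52, taken from the shares and range in section 1. Those come from separate studies of recurrent dizziness and are used here only as an assumed mix.

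The shift is the sum over diagnoses of (difference in share between arms) × (mean change). With V the between-diagnosis variance and 39 per arm, its SD is √(2V/39).

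| u | V | SD of shift | Chance of a shift of 0.75 or more, either direction (simulated, 200,000 runs) |
|---|---|---|---|
| 10 | 4.56 | 0.48 | 13% |
| 31 | 2.93 | 0.39 | 6% |
| 52 | 2.16 | 0.33 | 3% |

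The threshold of 0.75 is 0.15 × 5, and 0.75/3.63 = 21% of the planned effect.

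The two scales connect. With 4.84² = 23.4, the implied R² runs from 2.16/(2.16 + 23.4) = 8% to 4.56/(4.56 + 23.4) = 16%. A 5-point gap therefore belongs to the upper half of the table in step 2.

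**4. Would the covariate rule catch it?** Suppose it were stretched to cover diagnosis. With an equal mix, the SD of the between-arm difference in one share is √(2 × ⅓ × ⅔ / 39) = 10.7 points. A two-sided 5% test would miss differences below about 1.96 × 10.7 = 21 points.

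**The case against.** **Nothing is invalid.** This stands. A reader might infer that the primary estimate is biased. Over repeated randomisations it is not: the standard error already allows for chance imbalance, and type I error without the diagnosis term was 4.9% in simulation. The shift is conditional on the allocation that happens to occur, and it is as likely to favour placebo as GJD.

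**Prognosis is not shown.** This also stands. Section 3 speaks of homogeneity and of an influence on the results, without saying that diagnosis predicts DHI change irrespective of treatment. Every participant must also share the liver-deficiency pattern. An assumed gap of 5 points exceeds both the planned effect and the planning SD, so it is generous. The size of the loss is therefore a range, and at R² of 2–5% it is small.

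**Site-only stratification is a legitimate choice.** A reader might infer that section 2.7 is itself at fault. The document does not support that. Site by diagnosis would make 4 × 3 = 12 cells averaging 78/12 = 6.5 patients, and incomplete blocks in such cells could loosen the balance of arm sizes that blocking is there to keep.

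**Large imbalances are common.** A reader might combine two figures: a 27–37% chance that some diagnosis share differs by 15 points or more, and the 0.75-point shift, and infer about a one-in-three risk of a 21% distortion. They do not belong together. The first counts a difference in any of the three shares; the second needs the equivalent of a 15-point swap between the two extreme diagnoses. Under the stated assumptions, the chance of a shift that large is 3–13%.

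**The article is condensed.** The full protocol may say more, and an ANCOVA described with only categorical terms may be shorthand. But section 2.14 states a specific list of terms and a specific rule for adding to it, and neither admits diagnosis. An interaction test would normally fit a diagnosis main effect, but that is not the model stated for the primary estimate.

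**Conclusion.** The point holds as a matter of efficiency and of protection against chance imbalance, not of validity. As section 2.14 is written, a three-level baseline classification that the protocol itself flags cannot adjust the treatment estimate, either directly or through the covariate rule.

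The benefit of adjusting depends on a quantity the document does not supply: about 1–2 power points if diagnosis explains 2–5% of the variance of DHI change, and about 4–8 points at 10–20%. The 3–13% chance of a shift of 0.75 points or more rests on the assumed 5-point gap, the placing of unknown cause midway, and the assumed case mix. If diagnosis predicts nothing, adjustment loses practically nothing, and that asymmetry is the main reason to make the change. The allocation scheme can stay as it is.

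**What to change.** In section 2.14, add diagnosis (three levels, as recorded before randomisation) as a fixed factor next to group and site in the primary and secondary ANCOVA, and in the rank ANCOVA where that is used. State that it is kept whatever its p-value and whatever the balance between arms.

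The cost is one line of wording and 2 degrees of freedom; no new data are needed. It should be done before unblinding, since adding the term afterwards would look data-driven. The interaction test can stay as a separate step, and section 2.7 needs no change on this account. If the full protocol already contains the term, the published list should be brought into line with it.
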